**Patient**	
**Baseline measurement (T = 0)**	Sex, age, diagnosis, form of supported housing, smoking and drinking habits **Questionnaires**: SFS, BSI/WHOQOL-BREF
**Measurements at the UMCU (In the intervention groups: prior to the start of intervention and 12 months after the start of intervention)**	Medication use, smoking, and drinking habits **Questionnaires**: SFS, BSI, WHOQoL-BREF, IPAQ-SF, Sint Hans Rating Scale, structured questionnaire to indicate physical complaints that may influence gait, structured medication questionnaire **Measurements**: VO_2_ max Åstrand Bike test (submaximal), posture and gait analysis with a real-time video camera and markerless motion capture, blood pressure, length, weight, waist circumference Blood tests retrieved from medical records: HbA1c, total cholesterol, LDL-cholesterol, HDL-cholesterol, triglycerides
**Online questionnaire measurement (T = 3, 6, 9, 12, 15, 18, 21)**	**Questionnaires**: SFS, BSI/WHOQOL-BREF

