### Statistical analyses

#### Sample size

The sample size is calculated for the primary outcome social functioning. For the SFS we assumed an intra-cluster correlation of 0.1, a between-level correlation of 0.8, and a standard deviation of 9 [34, 41]. The anticipated dropout rate is 30%, as physical activity interventions in mental health care have average dropout rates of 26.7% [19]. We performed simulations to determine the power of the trial design to demonstrate an increase of at least 3 points after one year in the SFS. With measurements on seven time points in 100 patients, the study will have a power of 0.93.

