### Data analysis

The primary analysis in this study evaluates if the Muva intervention improves social functioning in comparison to care as usual. This will be analyzed with a mixed-effects linear regression model taking into account clustering of outcome measurements within individuals and centers using random effects and possible confounding factors age, gender and diagnostic subgroups using fixed effects. In addition, we will include lifestyle habits and character traits of the mental health worker as dependent variables to analyze the association between the mental health workers’ characteristics and the outcome social functioning.

Modified intention-to-treat analysis will be done, but if patients move to a team of the supported housing organization without the Muva intervention or rehabilitation care stops within 3 months of intervention, patients will be analyzed in the control group since they will no longer receive the Muva intervention. Patients that drop out from the study, will be analyzed in the group they participated in.

Sensitivity analysis will be performed on cluster, attendance at intervention activities, and medication changes. Dropout analysis will be performed. Analysis will be done in IBM SPSS statistics 25 and R version 4.0.4, using a 95% confidence interval (*p* < 0.05).

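### Repeated SFS scores are handled by random effects for individuals and centers with no serial correlation named; if within-patient correlation fades over time, the primary standard error is too small, and a decaying residual term is a cheap safeguard

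*Protocol article*

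**What the plan says.** Under Data analysis, the primary comparison of Muva with usual care rests on one model: "This will be analyzed with a mixed-effects linear regression model". Dependence enters by "taking into account clustering of outcome measurements within individuals and centers using random effects", with age, gender and diagnostic subgroup as fixed effects. The section mentions no random slope and no residual correlation structure, and excludes neither.

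Under Sample size, "we assumed an intra-cluster correlation of 0.1, a between-level correlation of 0.8, and a standard deviation of 9" is the only statement about correlation. It gives single values that do not depend on the time between scores.

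Table 3 schedules the SFS at baseline and at "T = 3, 6, 9, 12, 15, 18, 21" months. Under Study design and setting, three areas start Muva one after another at three-month intervals and one area stays in the control condition throughout.

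**The concern.** A random intercept per patient, with independent residuals, splits a patient's score into a fixed level and noise that is fresh at each wave. The correlation between any two of that patient's scores is then the same whatever the gap. A center intercept is also constant over time, so it adds no dependence on lag. In a long-lasting illness that fluctuates, scores close in time may be more alike than scores far apart.

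The design makes this matter. In a stepped wedge, exposure is off in an early block and on in a late block, so the Muva contrast compares scores that are mostly far apart in time. Slow drift within patients over such blocks does not average out as independent noise would. A model that treats it as independent noise reports too small a standard error. The confidence interval and p-value of the primary analysis are at stake.

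The fault would lie at patient level. It needs no drift of any area over time.

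**Working it through.** **The plan's own figure.** The article reports simulated power of 0.93 for "an increase of at least 3 points after one year in the SFS". It does not give the shape of the effect over time or the dropout pattern, and what is meant by "a between-level correlation of 0.8" is open, so the figure cannot be reproduced uniquely. With constant correlation 0.8, an effect growing linearly to 3 points at one year and 30% gradual dropout, a closed form gives 0.70 to 0.96. Some variants come close: 0.913 with seven waves, and 0.932 to 0.939 with eight. The stated power is not in dispute here.

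**Inputs from the article.** SD 9, so total variance 81; intra-cluster correlation 0.1; 100 patients; four areas, one never exposed; waves at months 0, 3, …, 21.

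**Assumptions.** 25 patients per area; center means area; no dropout; fitted period effects; area variance constant over time and treated as known; normal reference distribution. Exposure is first seen either at months 6, 9, 12 (layout A: starts at 3, 6, 9 with the effect visible one wave later) or at months 3, 6, 9 (layout B).

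**Variance split.** Area 0.1 × 81 = 8.1; patient part 81 − 8.1 = 72.9.

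**Formulas.** For area wave means, the working covariance is W = 8.1·J + 72.9·C_w/25 and the true covariance is S = 8.1·J + 72.9·C/25. J is the all-ones matrix. C is the true within-patient correlation matrix, and C_w is the constant-correlation matrix with the average off-diagonal value of C. X holds the exposure and period columns, and sums run over the four areas.

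- Model SE² = the exposure element of A⁻¹, with A = Σ X′W⁻¹X.
- True SE² = the exposure element of A⁻¹(Σ X′W⁻¹SW⁻¹X)A⁻¹.
- Type I error = 2Φ(−1.96 × model SE / true SE).

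**Average correlation for the intercept model.** With 0.8 per wave, the mean over the 28 pairs of waves is (7×0.8 + 6×0.64 + 5×0.512 + 4×0.4096 + 3×0.3277 + 2×0.2621 + 0.2097)/28 = 15.36/28 = 0.548. For a mix of 0.5 stable, 0.3 fading and 0.2 noise it is 0.5 + 0.3×0.548 = 0.665. For 0.6/0.2/0.2 it is 0.6 + 0.2×0.548 = 0.710.

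**Results, intercept-only model.**

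| True within-patient correlation | At 3 → 21 months | Model SE / true SE, layout A | Type I, A | Type I, B |
|---|---|---|---|---|
| Constant 0.8 | 0.80 → 0.80 | 0.518 / 0.518 | 5.0% | 5.0% |
| Mix 0.6/0.2/0.2 | 0.76 → 0.64 | 0.623 / 0.718 | 8.9% | 8.2% |
| Mix 0.5/0.3/0.2 | 0.74 → 0.56 | 0.669 / 0.799 | 10.1% | 9.1% |
| Pure AR(1), 0.8 | 0.80 → 0.21 | 0.774 / 1.110 | 17.2% | 15.1% |

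Check of the last row: 1.96 × 0.774/1.110 = 1.367, and 2Φ(−1.367) = 0.172.

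**Other layouts and decay patterns.** A separate calculation that included a seven-wave layout gave ratios of model to true SE of 0.70 to 0.87 and type I error of 8.7 to 16.8% with period effects. Under the same decays, a random slope in addition to the intercept gave 5.5 to 9.0%.

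**Does an area-by-period effect help?** In REML simulations (600 runs each), type I error without and with such an effect was 16.8% and 17.2% under AR(1), and 8.8% and 9.2% under the 0.5/0.3/0.2 mix. It did not help. Constant-correlation runs (400) gave 6.5% and 3.5%.

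**The remedy.** A patient intercept plus an exponentially decaying residual, without a separate noise term, gives type I error of 5.0 to 5.5% in every row and both layouts. Under constant correlation its SE stays at 0.518. Under AR(1) the true SE falls from 1.110 to 0.728, about a third.

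**The case against.** The strongest case on the other side is that the article does not commit to what is being criticised. It does not say that the random effects are intercepts, and a random slope would remove much of the inflation. Covariance structure is a detail that an article commonly leaves to the analysis plan. No decay is given anywhere, and on the one correlation stated the model is correct. The 17% figure takes 0.8 as an adjacent-wave value and assumes no stable patient component, so that correlation drops to 0.8⁷ = 0.21 over 21 months. That is strong for patients included for limitations lasting at least two years. Table 1 is not shown, the start months are assumed, and "The anticipated dropout rate is 30"% is left out of the calculation.

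Much of this stands. A reader might infer that the model has random effects for individuals only, that it forces equal correlation, or that its interval is too narrow. The text supports none of these as fact: centers are named too, slopes are not excluded, and the narrowing needs a decay that the article does not give.

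Two things remain. The article does more than stay silent: it names random effects at two grouping levels as the means of handling dependence, and pairs this with a correlation that does not vary with lag. Random intercepts are the natural reading of both. And the inflation does not depend on the extreme case: a fall from 0.76 to 0.64 over the study already gives 8 to 9%. The noise component does not undo the remedy either, since the simple decaying residual holds type I error near 5% in the mixed cases too.

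**Conclusion.** The point holds conditionally. Under constant within-patient correlation the planned interval is correct. If the final model uses random intercepts only and the SFS correlation fades with time, the model-based standard error is too small even with stable areas. Type I error is then about 8 to 10% under mild decay and 15 to 17% under pure AR(1) with 0.8 between adjacent waves. These sizes rest on the assumed decays, equal areas, eight waves, fitted period effects, no dropout and assumed start months. They leave aside the separate difficulty of having only four areas. The article does not show that the correlation fades, so this is a cheap improvement to the stated method and not an error in it.

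**What to change.** State in the primary analysis that the model has random intercepts for individual and center plus a within-patient residual correlation that decays with the time between waves, for example continuous-time AR(1) or exponential, with a separate noise (nugget) term if it can be estimated. Fix this before the data are examined, and report the intercept-only fit as a sensitivity analysis. R, which the trial already plans to use, can fit such a model.

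The cost is a sentence in the plan, one or two extra parameters and possibly some convergence checks. They would be estimated from at most 100 × 8 = 800 scores, fewer after dropout. If the correlation fades mildly, the reported interval widens: under the 0.5/0.3/0.2 mix in layout A the model SE goes from 0.669 to 0.731, about 9%, because the narrower interval was not honest. If the correlation is constant, almost nothing is lost.

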All teams of the supported housing organization (*n* = 30) will be invited to participate in the study. Teams in four different areas of Utrecht will be chosen to participate to prevent spillover effects and contamination since teams work closely together in these areas. Every area will form a cluster. Three clusters will start the intervention in a stepped wedged order, within intervals of three months, and one cluster will remain the control group during the study period (Table 1). To determine which area is allocated to which cluster to start the intervention, a simple randomization method is performed by drawing lots. Hence, randomization is done at cluster level and not at patient level. Randomization at patient level is not possible since teams deliver equal rehabilitation care to the patients of their team. Given the stepped wedge design and the vulnerable patient group, for whom continuity of research team is desired, participants and the research team know when each cluster will crossover from unexposed to the exposed period, also reducing the possibility of drop-out. Nevertheless, to reduce rater bias the final measurement at the 21th month of the study, will be performed blind to the intervention exposure duration (Table 1).

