#### Care as usual

During the control phase, patients receive care as usual. Care as usual consists of rehabilitation care focused on housing, (voluntary) work, and supporting patients to live independently. To stimulate an active control condition during the study period, there will be a general healthy lifestyle campaign at the supported housing organization that also targets the control group. In this campaign, several news messages on a healthy lifestyle will be posted on the organizations’ website targeting the mental health workers, but there will be no specific physical activity intervention targeting the patients. Next to the care from the supported housing organization, patients receive psychiatric care from their general practitioner or psychiatrist. This psychiatric care can consist of pharmacological treatment, psychotherapy, and a yearly somatic screening and medication review.

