## Outcomes and measurements

### Patients

#### Primary outcome

The primary outcome is social functioning as measured by the Social Functioning Scale (SFS) [40]. The SFS consists of seven domains of which we will use the domains social withdrawal, interpersonal communication, independency performance, independency competence, and recreation. We will not use the domains social interaction and work because due to the COVID-19 pandemic restrictions and lockdowns options for day programs (work) and social interaction in restaurants, cinemas and nightlife might be limited.

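### The primary mixed model as described has no calendar-period term, so in this stepped wedge part of any common drift in social functioning would be credited to Muva

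*Protocol article*

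**What the plan says.** The design (Study design and setting) is a stepped wedge over four areas: "Three clusters will start the intervention in a stepped wedged order, within intervals of three months, and one cluster will remain the control group". The primary analysis (Data analysis) is a linear mixed model covering "clustering of outcome measurements within individuals and centers using random effects and possible confounding factors age, gender and diagnostic subgroups using fixed effects". The supporting analyses do not deal with time either: "Sensitivity analysis will be performed on cluster, attendance at intervention activities, and medication changes".

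The article itself points to influences that could reach all areas at once. Two SFS domains were dropped because "due to the COVID-19 pandemic restrictions and lockdowns options for day programs (work) and social interaction in restaurants, cinemas and nightlife might be limited" (Primary outcome). During the study "there will be a general healthy lifestyle campaign at the supported housing organization that also targets the control group" (Care as usual).

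For the sample size, "we assumed an intra-cluster correlation of 0.1, a between-level correlation of 0.8, and a standard deviation of 9", and the aim is to "demonstrate an increase of at least 3 points after one year in the SFS". The stated power, obtained by simulation, is 0.93 for 100 patients and seven time points.

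**The concern.** The text names the confounders to be adjusted for and leaves out the one that the design creates. Age, gender and diagnosis hardly change within a person over 21 months, so they cannot distort a within-person contrast in the way that calendar time can. With random intercepts and no period term, the treatment coefficient is largely a before-after contrast within areas and persons. A common upward drift, for example as restrictions ease, would look like benefit. A downward drift would hide benefit. Both the primary estimate and its 5% test are at stake.

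**Working it through.** **The plan's own figure.** The power of 0.93 cannot be reproduced uniquely. It was simulated, the 0.8 correlation is not defined, and Table 1 is not shown. Configurations with and without period terms both come close:
- With period: 0.916 (eight occasions, crossover at 3/6/9, 70 patients, 0.8 within person, effect building over 12 months) and 0.947 (eight occasions, 6/9/12, 100 patients, same reading).
- Without period: 0.914 and 0.928 (eight occasions, 3/6/9 and 6/9/12, 100 patients, 0.8 as cluster autocorrelation, immediate effect).

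So the figure does not show whether the simulation included period.

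**Inputs for the bias.** From Sample size: SD 9 (variance 81) and ICC 0.1, so area variance is 8.1. Reading 0.8 as the within-person correlation, area plus person variance is 0.8 × 81 = 64.8. Person variance is then 56.7 and residual variance 16.2. With 100/4 = 25 patients per area, an area mean has residual variance 16.2/25 = 0.648 and intercept variance 8.1 + 56.7/25 = 10.37. Because the intercept variance is so much larger, the estimate is almost purely within-area.

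Assumed: eight occasions (months 0 to 21, as in Table 3), crossover at months 3, 6 and 9 with exposure counted from the next occasion, an immediate effect and no dropout. The areas then have k = 6, 5, 4 and 0 exposed occasions of 8.

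**No period term.** Each area's weight is k(8−k)/8 = 1.5, 1.875, 2 and 0, total 5.375. The never-treated area has weight zero, so it cannot correct a trend in this model.
- Linear drift: in each crossing area, exposed occasions lie on average 4 three-month steps after control ones. The share credited is 4/7 = 57%. With seven occasions it is 3.5/7 = 50%.
- Step at month 9: the exposed-minus-control differences are 5/6, 1 and 3/4. The share is (1.5 × 5/6 + 1.875 × 1 + 2 × 3/4)/5.375 = 4.625/5.375 = 86%.
- SE = √(0.648/5.375) = 0.35.

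**False positives with no true effect.** A 3-point drift gives 1.71 points and z = 1.71/0.347 = 4.9, so rejection is about 99.9%. A 1-point drift gives 0.57 points and z = 1.64, so rejection is Φ(1.64 − 1.96) ≈ 38%. In 1,000 simulated trials the rates were 0.999 and 0.379.

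**With categorical period terms.** The bias is 0. The treatment variation left after removing area and period means is 15 − 9.625 − 10.25 + 7.031 = 2.156, so SE = √(0.648/2.156) = 0.55, a ratio of about 1.57.

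**Range.** I varied crossover (0/3/6, 3/6/9, 6/9/12), the number of occasions (seven or eight), and whether the crossover occasion counts as exposed.
- Low end: seven occasions from month 3, crossover at 0/3/6 counted as exposed at once. Only one area then crosses within the data. The share is 48% and SE about 0.85, close to √(0.648/0.857) = 0.87. Rejection is about 9% (1 point) and 39% (3 points).
- High end: eight occasions, exposure from the occasion after months 6/9/12. The weights are 1.875 + 2 + 1.875 = 5.75 and SE = √(0.648/5.75) = 0.34. Rejection is about 40% and 99.9%.
- Overall: 48-57% of a linear drift, 70-92% of a month-9 step, SE ratio 1.15 to 1.6.

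Against the target effect: a drift of 3 points per year is 5.25 points over 21 months, and 57% of that is 2.99, about the whole 3-point effect.

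**The case against.** The strongest reply is that the sentence is a journal summary, not a model formula. It does not list the treatment indicator either, so a missing time term need not mean that time is excluded, and a fuller plan may contain it. That limits the point to the model as described, and nothing here shows that the final analysis will omit period. It does not dispose of the point. Treatment is implied by the stated comparison with usual care, whereas nothing in the article implies time, and the text does commit to named adjustment factors.

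The evidence for drift is also thinner than it may look. The most COVID-sensitive SFS domains were removed, though recreation and social withdrawal remain. The lifestyle campaign consists of website messages aimed at workers, and no onset within the study is given, so a trend from it is only inferred.

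The figures depend on assumptions. If the 3 points are an immediate effect, a power of 0.93 implies SE = 3/(1.96 + 1.476) = 0.87. Biases of 1.71 and 0.57 points would then be declared significant in about 50% and 10% of trials. That is still inflated, but far from 99.9% and 38%.

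A reader might infer three stronger things, which the article does not support:
- that all secular change is counted as Muva effect (the share is about 48-92%);
- that a false-positive result is near certain (that needs a sizeable drift and a near-worst-case design reading);
- that the power simulation left out period (0.93 fits either way).

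**Conclusion.** The point stands for the model as described: it omits the adjustment that this design needs, and the never-treated area helps only once period is modelled. The bias is conditional on a common drift. The drift sizes are hypothetical, and the error rates hold for 0.8 read as the within-person correlation. With 0.8 read as both cluster and individual autocorrelation, the SE without period terms is larger (0.64 against 0.35 in the eight-occasion, 3/6/9 design), so false positives are fewer. For a drift of 1 point per year they are 34% against 82%. The bias itself hardly changes (0.99 against 1.00 points). With no drift, the omission does not bias the estimate. Since the size of any drift cannot be known beforehand, this should be corrected before analysis.

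**What to change.** Add measurement occasion (calendar period) as a fixed effect in the primary model and in every secondary model that uses the stepped comparison, and report the effect as adjusted for period. Categorical occasion is preferable because it removes any common trend whatever its shape. Other forms of time adjustment are possible but rely on the assumed shape.

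The text change is one line. The cost is precision: the SE rises about 1.15 to 1.6 times under the assumptions above, and up to about 1.9 times if the effect builds over 12 months. The sponsor should therefore confirm that 0.93 comes from the period-adjusted model, or restate it, and define the 0.8 correlation. The definition matters: with eight occasions, crossover at 3/6/9, 100 patients and a 12-month build-up, period-adjusted power is 0.976 if 0.8 is the within-person correlation. It is 0.580 if 0.8 is both the cluster and the individual autocorrelation.

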### Methods

#### Study design and setting

This study is a pragmatic stepped wedge cluster randomized controlled trial that will be conducted at supported housing organization Lister and the University Medical Centre Utrecht (UMCU) in the Netherlands. This design allows us to implement the intervention sequentially in the participating teams and to study the effects of the Muva intervention.

A supported housing organization is an organization that supports people with SMI in their rehabilitation by giving assistance in several domains in patients’ lives such as housing, daily activities, (voluntary) work, building a social network and finances in order to promote independency. Within this setting, they do not provide psychiatric treatment, this is provided by the general practitioner or a psychiatrist from another organization. Patients have a key mental health worker, with a mental health degree of a university in applied sciences, who is responsible for the guidance plan and the rehabilitation support. This worker has guidance meetings with the patient for at least once a week, but more frequently if the condition of the patient requires more support. The patient population of Lister is diverse with patients living independently and receiving ambulatory care, patients who live in small assisted living facilitations and patients who live in a (group) house with 24 h care.

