### Study population

We will recruit 100 patients and their mental health workers. All participants will be informed about the study and asked for consent. Patients are included if they are ≥ 16 years old, diagnosed with a severe mental illness (i.e., a psychiatric disorder classified by the DSM-5 causing serious limitations in psychosocial functioning for a duration of ≥ 2 years), and can give informed consent and read and speak Dutch. Patients are not eligible for inclusion if their psychiatric condition hinders informed consent or/and participation in the intervention according to their mental health workers.

Mental health workers are included when they can give informed consent and read and speak Dutch.

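### Form of supported housing is collected at T=0 but left out of the named adjustment set, so the worker-characteristics association with social functioning may be confounded by care setting

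*Protocol article*

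**What the plan says.** All places are in the protocol article.

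- **Study design and setting** describes the organization's population: "The patient population of Lister is diverse with patients living independently and receiving ambulatory care", others in small assisted living, and "patients who live in a (group) house with 24 h care".
- **Study population** sets criteria on age, diagnosis, consent and language ("can give informed consent and read and speak Dutch"). It does not mention housing.
- **Table 3**, patient baseline row, records "Sex, age, diagnosis, form of supported housing, smoking and drinking habits".
- **Primary outcome** keeps five SFS domains, among them "independency performance, independency competence, and recreation".
- **Data analysis** describes a linear mixed model with "clustering of outcome measurements within individuals and centers using random effects" and fixed effects for "possible confounding factors age, gender and diagnostic subgroups using fixed effects". The next sentence adds the worker's lifestyle habits and character traits. It calls them dependent variables; I read this as explanatory variables, since it names social functioning as the outcome. The sensitivity analyses cover cluster, attendance and medication changes.

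**The concern.** Three of the T=0 patient variables (sex, age, diagnosis) go into the model. Form of housing stands beside them in Table 3 and does not.

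For the worker question this matters more than for the treatment question. Key workers belong to teams and were not allocated to patients at random, and their lifestyle and personality are measured once, at baseline. The worker coefficient therefore rests on comparisons between patients, and neither randomization nor within-patient change protects it. Housing form plausibly tracks how much support a patient needs, and two of the five retained SFS domains concern independence.

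If workers with healthier habits or higher conscientiousness happen to serve the more independent patients, a positive association would appear with no worker effect at all. That would be read as support for the hypothesis in Objectives, repeated in the Discussion, that such workers contribute more to their patients' active lifestyle.

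**Working it through.** **The plan's own figure.** The protocol gives no figure for the worker association. Its power of 0.93 is for the treatment comparison and is not in question here.

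**Inputs from the protocol (Sample size):** SD of SFS 9, intra-cluster correlation 0.1, between-level correlation 0.8, 100 patients, target effect 3 points.

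**Assumed inputs (not in the documents):** two settings with half the patients in each; an SFS gap of 4.5 to 9 points (0.5 to 1 SD); a worker-trait gap of 0.3 to 0.5 SD.

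**Step 1: spurious slope with no true worker effect.** With a setting indicator of variance 0.5 × 0.5 = 0.25 and the trait in SD units, the slope is 0.25 × (trait gap) × (SFS gap).

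- Low end: 0.25 × 0.3 × 4.5 = 0.34 SFS points per SD of trait.
- High end: 0.25 × 0.5 × 9 = 1.13.
- Either gap zero: 0.

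A large simulated sample gave 0.33 and 1.13 unadjusted, and about 0 after adding setting.

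**Step 2: three settings and a center random effect.** With three equally common, evenly spaced settings and trait-housing correlation r, the slope is r × (gap/2) × √(2/3). For gap 9 and r 0.4 this is 0.4 × 4.5 × 0.816 = 1.47; for gap 4.5 and r 0.2 it is 0.2 × 2.25 × 0.816 = 0.37.

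The correlations 0.2 to 0.4 are somewhat stronger than in step 1, where a trait gap d between equal halves means r = d/2, that is 0.15 to 0.25.

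A simulation used 100 patients with one SFS value each, 4 or 12 teams, a team random intercept with known variance components, and 1,500 runs per cell. Over gaps 4.5 to 9 and r 0.2 to 0.4:

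| | Without housing | With housing |
|---|---|---|
| Mean worker slope (true value 0) | 0.21 to 1.48 | within 0.07 of 0 |
| False-positive rate at nominal 5% | 6% to 41% | 4% to 6% |

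The team random intercept absorbs part of the bias. At gap 9 and r 0.4, the slope is 1.44 to 1.48 when housing is unrelated to team, and 0.91 to 1.09 when 80% of patients share their team's setting.

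**Step 3: a conditional ceiling.** The planning values imply a between-center variance of 0.1 × 81 = 8.1. If centers are teams and setting follows team completely, 0.25 × gap² cannot exceed 8.1, so the gap is at most √32.4 = 5.7 points. The high end of step 1 is then 0.25 × 0.5 × 5.7 = 0.71, before absorption by the random effect.

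**Step 4: the randomized Muva contrast.** I computed the generalized least squares weight of a constant level shift in the control area. There were four areas of 25 patients, three crossing over, 7 or 8 time points and period effects, with the 0.8 read as the within-patient correlation. The weight is 0.01 to 0.02 in absolute value. Even if the whole control area sat 9 points away from the others, the contrast would move by at most about 9 × 0.02 = 0.18 points, against a target of 3.

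**The case against.** The strongest reply is that the quoted covariate list stands in the sentence on the primary treatment model, where housing adds almost nothing, while the worker sentence carries no list of its own. Covariates for a supplementary association could be left to the analysis plan. This stands in part. But the worker sentence reads as an addition to the model just described, so the natural reading is that it inherits the named set. A variable already collected at baseline, and absent from both that set and the sensitivity analyses, is a concrete omission.

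A reader might infer that the association *is* confounded, or that the eligibility criteria deliberately span all settings. The documents support neither. Confounding needs housing to relate to both SFS and worker traits, and neither relation is given. The range of settings describes the organization's whole population; the criteria leave housing unrestricted, and the mix in the participating teams is not stated.

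The size also rests on choices that lean upward. Equal halves maximize the 0.25 factor, and step 1 ignores the center random effect and the adjustment for age, gender and diagnosis. Because centers are not defined as teams or areas, the share absorbed is unknown.

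Finally, housing at T=0 may partly be a result of the worker's earlier rehabilitation work. The Background cites a study linking worker conscientiousness to better self-reliance in patients, and the organization's support aims at independence. Adjustment could then remove part of the association sought. This objection holds, and it is why both estimates should be reported.

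**Conclusion.** The point holds as a risk to the worker-characteristics analysis only. Under the labelled assumptions the spurious slope is about 0.3 to 1.1 SFS points per SD of worker trait before the center random effect takes its share, and zero if housing is unrelated to either SFS or worker traits. The upper end would be sizeable beside the 3-point treatment target, but it needs a full 1 SD difference in SFS between settings.

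A reader might also infer that the main trial result is biased by care setting. It is not materially so: repeated measures within patients leave a level difference between areas a weight of only about 0.01 to 0.02. This is a small improvement to a secondary, observational analysis, not a flaw in the primary comparison.

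**What to change.** In the worker-characteristics model, add form of supported housing at T=0 (independent with ambulatory care, small assisted living, house with 24 h care) as a fixed effect. Prespecify that the worker estimate is reported both with and without it, and say that a difference between the two may reflect confounding by setting or adjustment for something the worker has already influenced.

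Adding housing to the primary treatment model is optional and gains little.

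The cost is a sentence in the analysis plan and about two degrees of freedom. No new data are needed, and fixing the choice now avoids picking a covariate after the results are seen.
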